### Interventions

To compare the effects of CBT in GDM patients, a control intervention—a conventional lifestyle intervention—will be provided. Patient education will be provided to the control group via oral communications from endocrinologists. The control group will also receive patient education, which will include disease-related knowledge, lifestyle modification, complication prevention, and other topics, but only during each follow-up.

Interventions will be delivered by WeChat MiniApp: “CBT GDM” (developed by Hangzhou Kang Sheng Health Consulting CO., LTD). This includes 5 sessions. The contents are designed and reviewed by endocrinologists and psychiatrists from the First People’s Hospital of Kunshan affiliated with Jiangsu University, Kunshan, Jiangsu Province, China. Participants will study according to a learning schedule which is divided into a strong intervention period (1–3 weeks) and a regular intervention period (4–12 months) (see Fig. 1).

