**Methods:**

This trial is designed as a prospective randomized controlled trial, which enrolled the patients diagnosed with GDM in First People’s Hospital of Kunshan affiliated with Jiangsu University from September 2021 to March 2023 with a 3-month follow-up. The specific randomization method was established and implemented through the central randomization system of EDC clinical trials. The percentage of all blood glucose levels collected within the normal range between the two groups at baseline, during the intervention period, and postpartum infant and maternal outcomes will be measured. Summary statistics for continuous variables will include the number of subjects, mean, median, SD, or the standard error, minimum, and maximum. The chi-square test, *t* test, and paired-sample *t* test were used for statistical analysis of differences between groups.

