### Eligibility criteria

#### Inclusion criteria

Patients’ inclusion criteria will be as follows: (1) age from 18 to 45 years old; (2) pregnant women who completed oral glucose tolerance tests (OGTT) at 24–28 gestational weeks; (3) meet diagnostic criteria of GDM and has not received pharmacological therapy; (4) no difficulty in using smartphones, basic Chinese reading and writing skills, basic calculation skills; (5) agree to sign the informed consent form.

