### Outcomes

#### Primary outcome measures

The primary endpoint is the percentage of fasting blood glucose, which is defined as the percentage of blood glucose levels within a normal range [17]. Glucose monitoring data is collected twice weekly after enrollment [time frame: from randomization (day 0) to V5 (week 12) for a total of 3 months of treatment]. The selected examination days shall be at least 2 days apart. Each examination day should contain the following self-monitoring data.

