### Data collection and management

#### Data collection

Data will be collected utilizing EDC at study site. Data collection takes place at seven points: baseline, day 1, day 14 (± 2), day 28 (± 2), day 56 (± 2), day 84 (± 2) during intervention period, and day 42 (± 2) post-partum. Collected data will be stored in the form of an electronic case report form. The clinical research coordinator (CRC) will complete the electronic case report form. The investigators will be informed of any changes made by CRC and system/edit check automatically done by the system. Authorized investigators will be permitted to access the study computers and evaluate the data throughout the study. If any missing data is detected via the EDC system, the researcher will contact the participants on the telephone.

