### Statistical methods

#### Statistical methods for primary and secondary outcomes

Categorical variables will be expressed in numerical values with their respective percentages and compared using the chi-squared test at baseline. Continuous variables will be expressed as mean ± SD and compared using the *t*-test. The significance of primary and secondary endpoints will be evaluated with the paired-samples *t*-test. A *p*-value < 0.05 indicates statistical significance. All data will be analyzed with the SPSS.

All patients who have received CBT for at least 4 weeks will be included in the full analysis set (FAS). Depending on the time investigated, the per-protocol (PP) analysis set will be made up of patients who complete the 6-month follow-up examinations. The FAS will be used as the basis for the primary analysis. If there is a discrepancy of greater than 10% between the FAS and PP samples, the analysis will be repeated for the PP analysis set. The safety population will include patients in the FAS. Unless otherwise noted, all analysis will be done in both the FAS and PP analysis sets. No additional analysis will be conducted.

There will be no replacement or imputation of missing values. All analysis will be based solely on observed cases. Patients who loss to follow-up will be considered to have dropped out of therapy. Only the PP patients will be used in a sensitivity analysis to test the impact of this assumption.

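### The regular CBT phase is stated in months (4–12), which cannot fit a 12-week treatment period ending at day 84; the per-protocol set likewise asks for a 6-month visit that is not scheduled

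*Protocol article*

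**What the plan says.** All references are to the protocol article.

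- **Interventions:** the learning schedule has "a strong intervention period (1–3 weeks) and a regular intervention period (4–12 months"), with a pointer to Fig. 1.
- **Primary outcome measures:** the time frame runs "from randomization (day 0) to V5 (week 12) for a total of 3 months of treatment".
- **Data collection:** seven points are listed: baseline, days 1, 14, 28 and 56, and then "day 84 (± 2) during intervention period, and day 42 (± 2) post-partum".
- **Abstract, Methods:** enrolment is described "with a 3-month follow-up".
- **Inclusion criteria:** participants are "pregnant women who completed oral glucose tolerance tests (OGTT) at 24–28 gestational weeks".
- **Statistical methods for primary and secondary outcomes:** the full analysis set rule reads "All patients who have received CBT for at least 4 weeks will be included in the full analysis set (FAS"). The per-protocol set consists of "patients who complete the 6-month follow-up examinations".

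**The concern.** The Interventions section is where the length of the tested treatment is defined, and it disagrees with every other statement of that length. A reader cannot tell whether women are assigned 12 weeks of CBT or up to a year of it.

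Three things depend on the answer:

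- the duration of CBT that the trial will report as tested;
- whether the day 42 post-partum assessment is made on or off treatment;
- what the analysis-set rules mean, since the full analysis set is defined by weeks of CBT received and the per-protocol set by a follow-up visit.

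The per-protocol rule brings in a further length, 6 months, that matches no listed visit. That set carries the planned sensitivity analysis on drop-out, so a rule that cannot be applied has a direct cost.

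**Working it through.** **Inputs.** Strong phase 1–3 weeks and regular phase 4–12 months (Interventions); treatment to week 12 (Primary outcome measures); last intervention-period visit at day 84 ± 2 and final visit at day 42 post-partum (Data collection); OGTT at 24–28 weeks' gestation (Inclusion criteria); 6-month examinations (Statistical methods). Conversion: 1 month = 30.44 days = 4.35 weeks.

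**The plan's own calendar.** 12 weeks × 7 = 84 days, which is the day 84 visit. 84 / 30.44 = 2.8 months, which is consistent with a nominal 3 months. The primary outcome section, the visit list and the abstract therefore agree with one another, and the Interventions text is the outlier.

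**Readings of the regular phase**

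| Reading | Calculation | Result against 12 weeks (84 days) |
|---|---|---|
| Both phases are durations | 1 + 4 × 4.35 = 18.4 weeks; 3 + 12 × 4.35 = 55.2 weeks | 6.4 to 43.2 weeks too long |
| Calendar, month 4 counted ordinally | starts after 3 × 30.44 = 91.3 days (week 13.0) | after the visit window closes at 84 + 2 = day 86 |
| Calendar, 4 months elapsed | starts at 4 × 30.44 = 121.8 days (week 17.4) | after day 86 |
| Mixed, week 4 to month 12 | ends at 12 × 30.44 = 365 days | far beyond day 84 |
| *Weeks* in place of *months* | 3 + 9 = 12 weeks: days 1–21, then 22–84 | exact, with no gap |

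Only on the literal calendar readings would weeks 4–12 have no scheduled CBT, which is 9 of 12 weeks (75%). On those readings only 3 weeks of CBT are scheduled before week 12, so the 4-week condition for the full analysis set could not be met inside the endpoint window.

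**Timing of the last listed visit.** Assume entry at 24–28 weeks' gestation and delivery at 37–42 weeks.

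- Delivery after entry: 37 − 28 = 9 weeks to 42 − 24 = 18 weeks.
- Adding 42 days (6 weeks): 15 to 24 weeks after entry, or 3.4 to 5.5 months.
- Six months = 6 × 30.44 / 7 = 26.1 weeks, so the last visit comes before the 6-month point in every case.
- Counted from delivery instead, the last visit is at 6 weeks, which is also not 6 months.

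**On or off treatment at that visit.** If CBT ends at week 12, a visit at 15–24 weeks is off treatment for everyone. If CBT lasts 18.4 weeks, it is on treatment for some women and off for others. If CBT lasts 55.2 weeks, it is on treatment for all.

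**The case against.** The strongest reply is that this is a one-word slip in a document whose other sections already give a consistent 12-week calendar, and that the primary endpoint is hardly affected. CBT given after week 12 cannot enter the endpoint. On the durations reading CBT covers the whole 12-week window, just as it does on the *weeks* reading. This stands, and it means that the 75% gap and the unreachable full analysis set rule belong only to a calendar reading that was probably not intended. They add no weight to the conclusion.

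Second, Fig. 1 is cited as the schedule and is not available here, so it may show the right unit. That limits what can be said about the intended schedule, but it does not rescue the sentence. If the figure shows weeks, the sentence is wrong; if it shows months, the figure conflicts with the primary outcome section and the visit list.

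Third, *weeks* is an inference. The session table includes post-partum diet and glucose content, and the study is said to run to March 2023, so some longer programme may have been in mind. This is fair, and the remedy should leave room for it. It does not remove the conflict with a treatment period stated as 3 months.

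Fourth, the visit list already separates the post-partum visit from the intervention period, which suggests off treatment. That is so, but the Interventions text says otherwise, and it is the section that defines the treatment.

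Finally, the 6-month per-protocol rule is a distinct fault that correcting the Interventions text would not cure. That is right. It is raised here because both faults come from study durations that do not agree. The entry range is also an assumption, since 24–28 weeks is the OGTT time and not an enrolment limit; later entry or preterm delivery would bring the last visit nearer to entry, still short of 6 months.

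**Conclusion.** The concern holds. The stated regular phase contradicts the 12-week treatment period on the duration, calendar and mixed readings. The excess is 6.4 to 43.2 weeks if the figures are durations; if they are calendar months, the regular phase starts after the last intervention-period visit has closed. Confidence in the textual contradiction is high. That *weeks* was meant is probable but unproven without Fig. 1.

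The consequence lies in the definition and reporting of the treatment and in the status of the post-partum assessment. The primary endpoint window and the sample size are not affected.

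Separately, the per-protocol set cannot be formed from the listed visits as written: none is at 6 months, and the last comes about 2 to 11 weeks before that point (26.1 − 24 = 2.1; 26.1 − 15 = 11.1), under the assumed entry and delivery ranges. Both faults should be corrected, and both can be corrected easily.

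**What to change.** 1. In Interventions, give the strong phase as weeks 1–3 and the regular phase as weeks 4–12, and check that Fig. 1 agrees.
2. If CBT is meant to continue after delivery, state how long it lasts, say that this part lies outside the primary endpoint window, and say whether the day 42 post-partum assessment counts as on treatment.
3. In Statistical methods, replace the 6-month requirement for the per-protocol set with a visit that exists: day 84 for the glucose outcomes, or day 42 post-partum if completion of the whole study is meant. Check that the 4-week CBT condition for the full analysis set refers to the same calendar.

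The cost is protocol wording only; no additional data or participants are needed.

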**Fig. 1 Fig1:**
[figure not shown]
CBT intervention schedule

**Table Tabb:** 

***Session 1 objectives:***	To explain the CBT process To describe the correlation between CBT and glucose management To learn mindfulness mediation
***Session 2 objectives:***	To discuss clinical knowledge regarding GDM, including the onset, development and outcome of hyperglycemia To set the goal of therapy of hyperglycemia and learn how to monitor To describe standard pharmacological and non-pharmacological treatments To identify the importance of postpartum glucose management To understand the importance of compliance
***Session 3 objectives:***	To evaluate the significance of diet in lipid-lowering To recognize high-risk foods (such as foods high in sugar) To recognize healthy foods (such as foods high in fiber) To create a postpartum diet plan To demonstrate self-management of healthy diets
***Section 4 objectives:***	To describe the relationship between emotion and blood glucose during pregnancy To recognize how to accept negative emotions To recognize how to praise for positive emotions To implement emotions management
***Section 5 objectives:***	To analyze poor glucose control cases To reflect on positive and negative behavioral changes

### Criteria for discontinuing or modifying allocated interventions

In the following circumstances, dropping out of the treatment program will be considered. At this point, participants will not be regarded to have dropped out of the experiment, and they will be eligible for protocol assessments unless they withdraw their consent for assessments (as described below).1) If the participant requests that the protocol treatment was discontinued.2) If the participant is unable to continue the protocol treatment due to adverse events.3) When the investigator believes that the risk of continuing the protocol treatment outweighs the benefits for any reason.4) When the investigator believes that continuing the protocol treatment is not appropriate for any other reasons.

### Adherence

Participants in the intervention group will use the WeChat MiniApp to log in and complete the intervention sessions according to the schedule. The completion of each session will be tracked by “GDM ASCVD.” The “clock-in” function in the “GDM ASCVD” app will provide positive and constructive feedback to participants to enhance adherence. Participants will be able to “clock in” from the dashboard to track their exercise and eating habits on a regular basis.

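### The per-protocol set and the therapy drop-out label rest on follow-up attendance, although session completion is tracked, so the per-protocol analysis does not show the effect in women who took the intervention.

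*Protocol article*

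**What the plan says.** Four parts of the protocol article bear on this.

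- **Interventions.** The CBT course is delivered through a WeChat MiniApp: "This includes 5 sessions". Controls receive oral education, and only at follow-up contacts.
- **Adherence.** "The completion of each session will be tracked by" the app, so exposure in the CBT arm is recorded session by session.
- **Criteria for discontinuing or modifying allocated interventions.** A woman may stop the programme and remain in the trial: "participants will not be regarded to have dropped out of the experiment, and they will be eligible for protocol assessments", unless she withdraws consent to be assessed.
- **Statistical methods for primary and secondary outcomes.** "All patients who have received CBT for at least 4 weeks will be included in the full analysis set (FAS"), and "The FAS will be used as the basis for the primary analysis". For the second set, "the per-protocol (PP) analysis set will be made up of patients who complete the 6-month follow-up examinations". Then: "Patients who loss to follow-up will be considered to have dropped out of therapy". And: "Only the PP patients will be used in a sensitivity analysis to test the impact of this assumption". The section also rules out any further analysis.

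**The concern.** The trial keeps a record of who did the sessions, and it distinguishes stopping treatment from leaving the trial. The analysis section drops both. It defines per-protocol status by attendance at examinations, and it infers therapy status from loss to follow-up.

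This matters for interpretation. A per-protocol result is normally read as the effect in participants who followed their assigned treatment. If the trial shows little difference, the team will want to know whether the app failed or was not used. A set defined by attendance cannot answer that, and the plan provides no other analysis that could.

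**Working it through.** **1. Apply the rules to particular women.**

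| Woman | Full analysis set | Per-protocol set | Therapy label by rule | What trial records would show |
|---|---|---|---|---|
| Uses CBT for 4 weeks, formally discontinues, attends all assessments | In | In | Not a drop-out | Stopped treatment |
| Opens few or no sessions, attends all assessments | Depends on what receiving CBT means | In, unless the set is nested in the full analysis set and receiving means sessions done | Not a drop-out | Little or no exposure |
| Finishes all five sessions over at least 4 weeks, then lost before the qualifying examination | In | Out | Drop-out | Completed the course |
| Control who attends the qualifying examination but misses earlier visits | Out if read literally; presumably meant to be in | In | Not a drop-out | Partial education |

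The first row needs no favourable reading. She meets the 4-week rule, the discontinuation section keeps her eligible for assessment, and she attends. Yet she is off treatment for 12 − 4 = 8 of the 12 weeks over which the primary outcome is collected. The third row shows the reverse error. The second row is open, because the article does not say whether receiving CBT means sessions completed or time with access to the app, nor whether one set lies inside the other.

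**2. Does correcting the 6-month visit remove the problem?** The data collection schedule ends at day 84 and day 42 postpartum, so the named examination matches no listed visit. Whichever visit replaces it, the set would still be defined by attendance.

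**3. Can the sensitivity analysis do its stated job?** The assumption under test is that women lost to follow-up had left therapy. The per-protocol set contains only women who completed follow-up. It therefore leaves out the women the assumption concerns, and says nothing about whether they had stopped. The session log could answer that directly.

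**4. Does attendance mean the same in both arms?** Controls are educated only at follow-up contacts, so attendance tracks their exposure fairly closely. CBT users work through the app between visits, so attendance says little about theirs.

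**5. Illustration of possible size.** Inputs from the Sample size section: 10-point difference, 80 per arm, one-sided 5%, power 0.80, 20% attrition.

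- The plan's own figure: 80 / (1 − 0.20) = 100 per arm, which reproduces. The 80 cannot be confirmed, because no SD or control-arm level is stated.
- SD implied if two means are compared: 10 / [(1.645 + 0.842) × √(2/80)] = 25.4 points.
- Assume a share q of the CBT women in the set did not complete the sessions and gained nothing. The difference becomes 10 × (1 − q): 9, 8 and 7 points for q = 10%, 20% and 30%.
- With 80 per arm and that SD, power = Φ[difference / (25.4 × √(2/80)) − 1.645], about 72%, 63% and 54%.

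Here q is assumed and the SD is back-solved. The trial was not sized on this set, which may hold fewer than 80 per arm.

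**The case against.** Several points on the other side are sound.

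- **The full analysis set has an exposure rule.** A reader might infer that women who did no sessions will be counted as treated. The article does not support that as a fact. If receiving CBT means doing sessions and the per-protocol set is nested, such a woman is in neither set. What stands is that she can be counted, and that the 4-week rule is not tied to the tracked sessions.
- **Controls are not guaranteed full exposure.** A reader might infer that every per-protocol control had the whole control intervention. The rule asks only for the 6-month examinations, so she could have missed the day 14, 28 or 56 visits. Only the weaker statement in step 4 holds.
- **A missed visit is not loss to follow-up.** Staff telephone participants when data are missing. Missing the qualifying examination can remove a woman from the set, but does not by itself make her a therapy drop-out.
- **The drop-out label has no stated effect on the primary estimate.** Analysis is on observed cases without imputation, and nothing removes labelled women from the full analysis set. The conflict with the discontinuation section is therefore largely one of definition.
- **A completer set may suit the stated purpose.** Comparing the two sets does show how far the estimate moves when lost women are left out. It still does not show whether they had stopped therapy.
- **Exposure thresholds often sit in a SAP.** That would excuse a missing threshold. Here the article states the rule itself, and bases it on attendance.

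**Conclusion.** The concern holds in a limited form. The per-protocol rule admits a documented treatment discontinuer and can admit women with little or no exposure. The drop-out rule mislabels a woman who finishes the course and is then lost. The per-protocol analysis therefore shows neither the effect in women who took the intervention nor the truth of the drop-out assumption.

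The size cannot be stated, because the article gives no completion rate. The fall from 10 points to 8 or 7 rests on an assumed 20% to 30% non-completion with no benefit at all from partial use. A reader might infer that the trial's main result is diluted or underpowered because of this definition. The documents do not support that: the primary analysis uses the full analysis set, and dilution from non-use would also appear in a correctly specified analysis of all randomised women. The fault affects how a sensitivity analysis is read. It should be corrected, but it does not undermine the primary comparison.

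**What to change.** In the statistical methods section:

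1. Define the per-protocol set as members of the full analysis set with a prespecified minimum of tracked sessions (CBT arm) or attended education contacts (control arm). The investigators should set the threshold before analysis. This presupposes a full analysis set that admits controls, which its present wording does not do literally.
2. State whether receiving CBT for at least 4 weeks means sessions done or time with access.
3. Take therapy status from the app log instead of inferring it from loss to follow-up, and reconcile this section with the discontinuation criteria.
4. Keep the per-protocol analysis as a sensitivity analysis.

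The cost is a reworded paragraph and use of a record the plan already says will be kept. First confirm which system holds it: the Interventions section calls the app CBT GDM, while the Adherence section names GDM ASCVD as the tracker. The downside is a smaller set, selected on adherence after randomisation, which is why it should stay secondary. A complier-average estimate is optional. It would need data on all randomised women, and partial use of the app may itself bring benefit, so its assumptions would need defending.
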